#### 6.9.5. Interim Efficacy Analysis (for interim safety analyses, see Section 6.9.4.1)

Under the study design assumptions, all participants will be followed for 36 months after the immunization phase with assessment for HIV infection occurring at six-month intervals. One interim efficacy analysis will be scheduled approximately 36 months after the beginning of the estimated 2-year accrual period, i.e. 36 months after the first enrollee completes the first visit. This time is estimated as the time at which the expected total patient exposure time is

approximately 2/3 of what it is expected to be at the end of the trial. Results from the interim analysis will be presented to the DSMB. The purpose of the interim analysis is to monitor the trial for early evidence of definitive efficacy. The following section outlines stopping rules assuming one interim efficacy analysis.

Two-sided O'Brien-Fleming error spending function boundary values for one interim analysis at 2/3 information time and at the end of the study period were determined using a Lan-DeMets spending function approach. Overall significance level was assumed to be 0.05. The software 'ld98.exe' that was used to calculate the values is described in Reboussin et al (60) and was downloaded from the University of Wisconsin website ([/www.medsch.wisc.edu/landemets/](http://www.medsch.wisc.edu/landemets/)). The absolute value for the two-sided O'Brien-Fleming error spending function boundary values is 2.5086 at 2/3 information time and 1.9929 at the end of the study period. If the timing of the interim analysis is changed from 2/3 information time due to practical considerations, then the boundary values will be recalculated.

The lower limit of the two-sided 95% confidence interval is used in the interim analysis to test the null hypothesis that vaccine efficacy is 30%. The method for determining repeated confidence intervals (61) draws upon the correspondence between statistical tests and confidence intervals. The lower limit of the two-sided 95% confidence interval for vaccine efficacy will be calculated as one minus the upper limit on the 95% confidence interval for the hazard ratio at the interim analyses. The upper limit of the two-sided 95% confidence interval for the hazard ratio will be determined using the O'Brien-Fleming boundary value that was computed for the analysis (i.e., 2.5086). At the interim analysis:

- If LL of 2-sided 95% CI for VE >30%, stop and reject the null hypothesis.

The null hypothesis for the final analysis will be that true vaccine efficacy is equal to 0%. The statistical test at the planned conclusion of the trial will be a 2-sided 5% level test of the hypothesis that the risk of infection is the same at any given time in the two treatment groups. The test statistic will be compared to the O'Brien-Fleming error spending function boundary values determined for the end of the study period.

If the null hypothesis at the interim analysis is accepted and after the final analysis:

- If  $|Z_{\text{final}}| \geq 1.9929$ , reject the null hypothesis.

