### **6.9.2. Sample Size, Accrual and Follow-up**

The target for recruitment is a total of 16,000 subjects. Individuals will be enrolled and randomly assigned to two study arms over approximately 2 years. The allocation ratio for the two study arms will be 1:1.

All participants will be followed for three years, after a 24-week immunization period, with assessment of HIV-1 infection occurring at semi-annual clinic visits. Power calculations are presented for a variety of assumptions. Sample size was determined using the conservative assumption that the annual HIV-1 seroincidence rate within the placebo arm will be approximately equal to the lower bound of the 95% confidence interval on incidence rates observed in studies within similar populations. A recent seroincidence cohort study of 20-40 year olds in Chon Buri Province found an incidence of 0.51/100 person-years, with a 95% confidence interval of 0.26 - 0.76/100 person-years. Among 20-30 year olds, the incidence was 0.68/100, with a CI lower bound of 0.34/100 P-Ys. Sample size calculations for this protocol assume an annual seroincidence of 0.34%, and that the rate of loss to follow-up will be 5% every 6 months including the vaccination phase. If the actual seroincidence rate is higher than the conservative estimate of 0.34%, then power will be higher. An exponential model is assumed for the time-to-infection data. In the study vaccine arm a piecewise relative hazard function was assumed in which vaccine efficacy was 25% during the 24-week immunization period and increased to 50% thereafter. Under these assumptions and with testing for an interim analysis and a final analysis as described in Section 6.9.3, a sample size of 16,000 is sufficient to allow power of 90.2% in an intent-to-treat analysis and 91.0% in a per-protocol analysis. A detailed explanation of sample size calculations can be found in Appendix 17.6.

The estimated dropout rate of 5% per 6 months is based on a cohort study carried out in Chon Buri Province during 1999-2001 (Benenson, et al., unpublished data). Assuming this loss

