to follow-up, we expect to accrue approximately 19,126 person-years of follow-up in each arm (vaccine and placebo) of the study, after the 24-week immunization period. As noted in Section 6.1, if the dropout rate during the vaccination phase exceeds 5%, additional subjects will be recruited and enrolled to achieve 15,200 volunteers completing the 24-week vaccination phase, unless the length of time necessary to achieve 15,200 volunteers is unacceptable. Extending the enrollment period will have the effect of increasing the average time of entry into the study. The length of follow-up (3 years) will not change. If we assume that individuals enter the study uniformly throughout the enrollment period, extending the enrollment period by a specified amount should move forward the approximate time of the interim analysis by half of the number of months enrollment was extended. However, the exact timing of the interim analysis will depend to some extent on practical considerations, such as availability of the DSMB for review of the interim analysis.

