Table 4 summarizes the final estimates of overall statistical power for varying hypothesized levels of true vaccine efficacy that are of practical interest. The final power estimation assumes that one interim analysis will be conducted at 2/3 information time. The null hypotheses for the interim and final analyses are as described above. Other provisions for the setup of the simulation exercise are the same as for the initial power estimation. By design, overall power is similar between the initial and final estimations for varying alternatives. When true vaccine efficacy is assumed to be 50% (with 25% in effect during the vaccination period), overall power is 90.2% and 91.0% for the intent-to-treat and per-protocol analyses, respectively. Given the strict testing criterion that is specified for the interim analysis, the probability is only 5.4% for detecting a statistically significance difference between the treatment groups in the early analysis (intent-to-treat) under this alternative. If the specification of the true vaccine efficacy is increased to 75%, (and 37.5% for the vaccination period), statistical power for the interim analysis is estimated to be 57.6% (intent-to-treat). Power is obviously negligible for interim testing (<1%) when true vaccine efficacy of 30% is considered, but the probability of accepting the null hypothesis in the interim analysis and subsequently rejecting the null hypothesis of 0% efficacy in the final analysis is 43.4% (intent-to-treat analysis) under this alternative.

**Table 4.** Final power calculations/Estimated overall power and estimated probability of rejecting the null hypothesis in the interim and final analyses with associated median estimates of vaccine efficacy (VE) and lower limit of the 2-sided 95% confidence interval (CI) for vaccine efficacy (VE) for varying levels of true vaccine efficacy (intent-to-treat ITT and per-protocol PP)

|                                               | Interim Analysis                                 |                        |                       | Final Analysis [1]                              |                        |                       | Overall Statistical Power [2] |
|-----------------------------------------------|--------------------------------------------------|------------------------|-----------------------|-------------------------------------------------|------------------------|-----------------------|-------------------------------|

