#### **17.6. Detailed Description of Sample Size Calculations**

Power calculations were performed through computer simulation of 10,000 data sets using the SAS system. Sample size was determined for the intent-to-treat analysis. The calculations assumed an annual sero-incidence of 0.34% and a rate of loss to follow-up of 5% every 6 months during the follow-up period, or a cumulative dropout rate of 30.2% over 3 years of follow-up plus the vaccination phase. The rate of 5% includes volunteers who remain available for follow-up but did not receive all vaccinations within the protocol-specified time periods. The same rate of 5% was assumed for both the intent-to-treat and per-protocol analyses, since it is difficult to project what part of the 5% will be from loss to follow-up and what part from non-compliance with the

vaccination schedule. Therefore the rate of 5% is an upper bound on loss to follow-up for the intent-to-treat analysis since this analysis includes individuals who do not comply with the vaccination schedule. In addition, it is assumed that 5% will be lost to follow-up during the 24-week vaccination period prior to the beginning of follow-up. Length of follow-up after the end of the vaccination period was assumed to be 3 years. An exponential model was assumed for the time-to-infection data and a uniform model was assumed for the time-to-dropout data. Vaccine efficacy was assumed to be 25% during the 6-month vaccination period and 50% thereafter.

For each of the 10,000 simulated datasets, a sample of specified size was generated with half belonging to the vaccine arm and half belonging to the placebo arm. For each individual, a time-to-infection variable was generated from an exponential distribution. An inverse transformation method was applied to a SAS uniform random variate. For individuals in the placebo arm, the exponential parameter was set equal to  $-\log(1-IR)$  where IR is the annual placebo sero-incidence rate. For each individual in the study vaccine arm, the exponential parameter was set equal to that in the placebo arm, multiplied by a factor of  $(1-VE)$ , where VE is the assumed vaccine efficacy. In the study vaccine arm, a piecewise relative hazard function was assumed in which VE was 25% over the 6-month vaccination period and increased to 50% during the follow-up period.

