Power was investigated with one interim analysis built into the study design. One interim analysis was planned for 36 months after the beginning of the accrual period, when approximately 2/3 of the follow-up information is expected to be available. Test statistics were compared to the O'Brien Fleming type boundary values in a spending function, Lan-DeMets, approach obtained from a program called 'ld98.exe' available from the University of Wisconsin website (<http://www.medsch.wisc.edu/landemets/>). O'Brien-Fleming boundary values were calculated for one interim analysis at 2/3 information time and at the end of the study period. Overall significance level was assumed to be 0.05. Power was defined as the frequency of rejecting the null hypotheses under the specified alternative value for vaccine efficacy. The null hypothesis was

rejected if it was rejected at the interim analysis, or accepted at the interim analysis and then rejected at the final analysis.

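### Month 36 yields about 0.61 of expected exposure, not 2/3, so the printed interim boundary and Table 4's early-stopping chances do not fit the scheduled look

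*Protocol*

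**What the plan says.** Protocol Section 6.9.5 sets the date: "One interim efficacy analysis will be scheduled approximately 36 months after the beginning of the estimated 2-year accrual period". It also gives the basis: "This time is estimated as the time at which the expected total patient exposure time is" about two thirds of its end-of-trial value. Section 17.6 repeats that month 36 is "when approximately 2/3 of the follow-up information is expected to be available".

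The boundaries of 2.5086 (interim) and 1.9929 (final) were computed for a look at 2/3. Section 6.9.5 prints 2.5086 inside the stopping rule and 1.9929 in the final test. It provides for new boundaries if practical considerations move the look away from 2/3.

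Table 4 in Section 6.9.3.1 gives interim rejection probabilities for the same 2/3 look. At 50% efficacy the intent-to-treat figure is 5.4%; at 75%, "statistical power for the interim analysis is estimated to be 57.6% (intent-to-treat").

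The inputs are in Section 6.9.2: "If we assume that individuals enter the study uniformly throughout the enrollment period"; "All participants will be followed for three years, after a 24-week immunization period, with assessment of HIV-1 infection occurring at semi-annual clinic visits"; and the assumption "that the rate of loss to follow-up will be 5% every 6 months including the vaccination phase". Section 17.6 turns the last into "a cumulative dropout rate of 30.2% over 3 years of follow-up plus the vaccination phase".

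**The concern.** If the last volunteer enters at month 24, time on study at month 36 runs from 1 to 3 years and averages 2.0, against about 3.5 planned. That is 0.57 before dropout. Dropout thins out later follow-up and so raises the fraction, but it is not obvious that it raises it to 0.67.

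The date, the boundary and the Table 4 probabilities are all tied to 2/3. If month 36 falls short, a look held exactly on schedule would use a boundary computed for more information than exists, and the DSMB would have been told that the look is more likely to stop the trial than it is. The recalculation clause would not obviously apply, because in the plan's own terms nothing has been moved away from 2/3.

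**Working it through.** **1. The protocol's other figures reproduce.**
- Cumulative dropout: 1 − 0.95^7 = 0.302.
- Person-years per arm after immunization: 8,000 × 0.5 × (0.95² + … + 0.95^7) = 4,000 × 4.7816 = 19,126, as stated.
- Infections: the yearly rate is −ln(1 − 0.0034) = 0.003406, so 8,000 × rate = 27.25 per arm per year of mean exposure. With 22,926 person-years per arm including vaccination, placebo = 78.1. Vaccine = 9.7 + 32.6, which rounds to 10 + 33 = 43. Both as stated.
- Boundary: the O'Brien-Fleming-type spending function is α(t) = 4[1 − Φ(2.2414/√t)]. At t = 2/3, α = 0.0121 and the boundary is 2.509, with 1.993 at the end. Both as stated.

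**2. Exposure at month 36.** With dropout of 30.2% spread uniformly over 3.5 years, as in the Section 17.6 simulation, mean retained exposure after *a* years is C(a) = a − 0.302a²/7.
- Full: C(3.5) = 3.5 − 0.5285 = 2.9715.
- Month 36: *a* is uniform on 1 to 3 years, with mean 2 and mean square 26/6 = 4.333. Mean C = 2 − 0.1870 = 1.8130.
- Fraction: 1.8130/2.9715 = **0.610**.

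Geometric or end-of-interval dropout also gives 0.61. Using 3.46 years in total (24 weeks plus 3 years) gives up to about 0.62. Two thirds is reached at month 38.2 to 38.5. To reach about 2/3 at month 36, accrual would have to last about 1.5 years (0.68).

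**3. Infections at month 36 (efficacy 25%/50%).** Weight exposure by the two-arm hazard: 1 + 0.75 in the first half-year, 1 + 0.5 afterwards. C(0.5) = 0.4892.
- Final total: 1.75 × 0.4892 + 1.5 × (2.9715 − 0.4892) = 4.5796.
- Occurred by month 36: 0.8561 + 1.5 × (1.8130 − 0.4892) = 2.8419, fraction 0.62.
- Detected: the last completed visit is at 1.0, 1.5, 2.0 or 2.5 years, a quarter of volunteers each. Mean C = 1.75 − 0.1456 = 1.6044, and 0.8561 + 1.5 × (1.6044 − 0.4892) = 2.5289, fraction **0.55**.
- Rounded up to the next visit, not yet held (1.5 to 3.0 years): mean C = 2.0181, fraction 0.69.

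**4. Interim rejection probabilities.** Infection counts per arm were simulated as Poisson. The rule is ln(V/P) + 2.5086 × √(1/V + 1/P) < ln 0.70, where V and P are the vaccine and placebo counts.

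| Intent-to-treat, month 36 | Expected P + V, VE 50% | Stop, VE 50% | Expected P + V, VE 75% | Stop, VE 75% |
|---|---|---|---|---|
| Table 4 | – | 5.4% | – | 57.6% |
| Occurred | 49.4 + 28.0 | 4.2% | 49.4 + 17.3 | 48% |
| Detected | 43.7 + 25.2 | 3.1% | 43.7 + 15.9 | 37% |
| Rounded up | 55.0 + 30.8 | 5.3% | 55.0 + 18.7 | 58.5% |

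The other dropout conventions lower these by up to 0.2 points at 50% and up to 3 points at 75%. As a check at 75% on occurred infections: ln(17.3/49.4) + 2.5086 × 0.2794 = −1.049 + 0.701 = −0.348, an upper hazard-ratio limit of 0.706, just on the wrong side of 0.70. A probability just under one half is what that implies.

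**5. Boundaries for the actual fraction.** The same spending function gives 2.64 (final 1.983) at 0.61 and 2.81 (final 1.974) at 0.55. With 2.81 on detected infections the stopping chances are about 1.4% and 25%.

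**6. Type I error.** If both looks tested zero efficacy at t = 0.55 with 2.5086 and 1.9929, overall alpha would be 0.0516. The interim in fact tests 30% efficacy, so it adds almost nothing under zero efficacy. The final test alone has 0.0463, and the true error stays below 0.05.

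**The case against.** The best defence is that the plan anchors on information as well as on the calendar. Section 6.9.3.1 places the look at 2/3 information, Table 4 is labelled for that look, the timing statements are hedged as approximate, Section 6.9.2 allows practical adjustment, and Section 6.9.5 allows new boundaries. On this reading Table 4 is right for the look it names, and the only error is an optimistic calendar estimate of a little over 2 months. Part of this stands: on the plan's stated measure, exposure, the shortfall is 0.61 against 0.67. The 0.55 comes from counting detected infections. That is the relevant quantity for a hazard-ratio test, but it is not the plan's definition.

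The defence does not remove the conflict. The recalculation clause is written for practical departures from 2/3, the plan takes month 36 to be 2/3, and the stopping rule prints 2.5086.

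Table 4 does match month 36 if each person's time is rounded up to the next visit, as the Section 17.6 discretization does for infection times. That may be how the figures arose, but the protocol does not say so. Infections credited to visits not yet held could not be in hand at the look.

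A reader might also infer that the trial's error rate or power is compromised. Step 6 shows that the error rate is not, and overall power stays near 90%, because almost all of it at the design alternative comes from the final test. Nor should the 2.81 boundary be carried over to the per-protocol analysis: its detected fraction at month 36 is only about 0.45, where the same function gives about 3.14.

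**Conclusion.** The statement that month 36 gives approximately 2/3 of the information is wrong under the protocol's own assumptions. Exposure is about 0.61 to 0.62, and detected intent-to-treat infections are about 0.55 of the total. Table 4's interim columns do not describe a look held then.

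At the design alternative of 50% efficacy the gap is small: 5.4% stated, against about 3% to 4% with 2.5086. It is material at 75% efficacy: 57.6% stated, against about 37% to 48% with 2.5086, or about 25% with the boundary for 0.55 on detected infections. The harm is an overstated chance of stopping early for a highly effective vaccine, and no more than that.

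This rests on uniform entry over exactly 2 years, 5% dropout per 6 months and 0.34% placebo incidence. Simulation error and the choice of dropout convention move the 75% figures by a few points but do not close the gap.

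**What to change.** Reconcile the calendar date with the information fraction in Sections 6.9.3.1, 6.9.5 and 17.6, in one of two ways.

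- **Keep month 36.** State the information as about 0.61 of exposure (about 0.55 of detected intent-to-treat infections). Replace the printed 2.5086 and 1.9929 with boundaries computed from the actual fraction at the look, and say how that fraction is measured. Restate Table 4's interim columns from infections that could be in hand at that date.
- **Keep 2/3.** Move the look to the time when 2/3 is projected: about month 38 on exposure, about month 41 on detected infections. Re-project it during the trial from pooled, blinded incidence and retention.

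A fixed trigger of 81 infections (2/3 of 121) is tempting but unsound. Follow-up is fixed at 3 years, so the final number of infections is not fixed, and Section 6.9.2 calls 0.34% conservative. At 0.68% incidence, 81 detected infections would arrive near month 27, at about a third of the eventual total.

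The cost is protocol and DSMB-charter wording plus one rerun of the interim simulations. The downside is a look some 2 to 5 months later, or a lower stated chance of early stopping. Sample size and final power do not change materially.

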#### **6.9.6. Interim Futility Analysis**

At each meeting of the DSMB a futility analysis will be considered by the DSMB based on operational issues. The parameters used to determine futility are as follows:

1. Too few subjects volunteer for the trial
2. Too few subjects complete vaccination
3. Too few subjects complete follow-up
4. Too few cases of infection occur in the placebo group to detect an effect, and
5. Operational issues that compromise trial execution

At each DSMB meeting the conditional power will be evaluated. If conditional power is less than 10% under both the protocol assumptions and for the current trend then study closure would be recommended. The recommendation would be tempered if a trend for viral load control was observed and the precision of the estimate is inadequate (99%CI width >1.2log).

#### 6.9.7. Additional Laboratory Studies and Data Analysis

RV144 assessed volunteer risk behavior at baseline and follow-up using a self-administered behavioral questionnaire. Based on this assessment, 89% of volunteers reported one or less sexual partners and less than 5% reported high risk behavior (96). Hepatitis B can be transmitted through percutaneous or sexual exposure. Hepatitis C transmission almost exclusively occurs after percutaneous exposure. These two infections are common in MSM and intravenous drug users. In addition, hepatitis C in intravenous drug users is associated with HIV infection. In Thailand, men who become HIV infected have a significantly higher rate of HCV infection (97). Herpes Simplex Virus – 2 (HSV-2) is also transmitted sexually and its prevalence is associated with past sexual activity. In addition, HSV-2 infection is associated with a two to fourfold increase risk of HIV acquisition (98). To better characterize a volunteer's behavioral risk classification during the trial and its impact on HIV acquisition and vaccine efficacy, we plan to analyze biomarkers (serology to HBV, Hepatitis C, HSV-2, syphilis) associated with HIV acquisition and high risk behavior using stored volunteer samples unlinked to any personal identifiers.

To evaluate whether pre-existing immunity against vaccine vector impacts on vaccine immune responses, we are also proposing to conduct anti-ALVAC antibody assay using stored volunteer samples.

The STEP study which tested a replicating defective Ad5 vector expressing HIV-1 Gag, Pol, and Nef found volunteers who received the vaccine and had high levels of pre-existing Ad5 antibody were at greater risk for acquiring HIV as compared to volunteers who received placebo (99). One possible mechanism for this enhancement in HIV infection is the preferential expansion by Adenovirus of memory CD4 T cell with mucosal homing phenotype that increases susceptibility to HIV infection in individuals with prior Adenovirus immunity (100). It is unclear whether this mechanism is specific to Adenovirus vector only or may apply to other non-replicating viral vectors. Analysis of RV144 result specifically did not show enhancement in HIV infection. However to exclude the possibility of uneven distribution of this potential confounder, we will conduct Ad5 antibody assay using archived samples.

Both Ad5 and anti-ALVAC antibodies will be determined using well established luciferas-based virus neutralization assay (101,102). Each assay will require 200ul of plasma. To determine distribution of baseline pre-existing Ad5 and anti-ALVAC antibodies, 200 random samples (100 placebos and 100 vaccinees) will be tested at baseline and 4 weeks post final vaccination.

As part of the pre-specified primary immunogenicity analysis, we have already conducted post vaccination CD4+ HIV-Specific intracellular cytokine staining (ICS), gp120 and p24 binding antibody; and lymphoproliferative assays on approximately 150 vaccine and 50 placebo recipients (96). Anti-ALVAC antibody assays will be conducted on the 150 individuals who received vaccine. To assess the impact of pre-existing anti-vector antibody on immunologic response, we intend to compare the proportion with ICS response and geometric mean binding antibody by presence or absence of pre-existing anti-ALVAC antibody.

To assess the impact of pre-existing on HIV acquisition, we intend to conduct a case control study comparing prevalence of baseline Ad5 and anti-ALVAC antibodies between volunteers who acquired HIV infection (case) and volunteers who remained free from HIV infection (controls). Controls will be matched to cases by gender, age and risk behavior at a 2:1 ratio.

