Viral load measurements will be compared between HIV-infected vaccine and placebo recipients. Statistical tests will be carried out comparing the  $\log_{10}$  viral load measurements obtained after the initial diagnosis of HIV infection at the set point (Section 6.7.1). A non-parametric Mann-Whitney test will be used for the comparison. The statistical power of a t-test for differences in the  $\log_{10}$  viral load measurements between HIV-infected vaccine and placebo recipients was calculated. The calculations assume that vaccine efficacy is 25% during the immunization period and 50% after complete immunization, and that three viral load measurements are obtained on every participant who becomes infected during the trial. Detectable differences are calculated for 2-sided non-parametric Mann-Whitney tests at a significance level of 0.05. Under the anticipated study design there are expected to be approximately 43 infected vaccinees and 78 infected placebo recipients, including 10 vaccinees and 13 placebo recipients who become infected before complete immunization. Table 5 shows minimum detectable differences in  $\log_{10}$  viral load for power of 80% and 90% for varying vaccine efficacy. Detectable differences were calculated using PASS 2000 with nonparametric adjustment to a t-test. Minimum detectable differences are presented for both an intent-to-treat analysis which includes those who become infected before full immunization, and also for a per-protocol analysis which excludes those who become infected during the immunization period. If vaccine efficacy is 50% and the viral loads in the two groups differ by 0.39  $\log_{10}$  or more, then this difference should be detectable with the current study design with at least 80% power.

**Table 5.** Detectable differences in HIV-1 viral load for 80% and 90% power – intent-to-treat and per-protocol analyses.

| Type of Analysis | VE  | Infected Vaccine Recipients (#) | Infected Placebo Recipients (#) | Detectable Difference |           |
|------------------|-----|---------------------------------|---------------------------------|-----------------------|-----------|
|                  |     |                                 |                                 | 80% Power             | 90% Power |
| ITT              | 0.3 | 57                              | 78                              | 0.36                  | 0.41      |

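### The case-control study compares only the prevalence of baseline Ad5 antibody, although its rationale is a finding about high levels; a titre comparison should be added beside it

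*Protocol*

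**What the plan says.** All of this is in Protocol section 6.9.7.

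- **Motivation.** In an earlier trial of an Ad5-vectored vaccine, volunteers who "had high levels of pre-existing Ad5 antibody were at greater risk for acquiring HIV". The possible mechanism is worded differently: it "increases susceptibility to HIV infection in individuals with prior Adenovirus immunity".
- **Purpose of the Ad5 assay.** "to exclude the possibility of uneven distribution of this potential confounder, we will conduct Ad5 antibody assay using archived samples".
- **Assay.** Both antibodies are measured with a luciferase-based virus neutralisation assay. The title of the cited Ad5 method (section 15, reference 102) describes it as quantifying antibody.
- **Distribution.** A separate component tests 200 random samples, 100 per arm, to describe how the two antibodies are distributed.
- **HIV acquisition.** "we intend to conduct a case control study comparing prevalence of baseline Ad5 and anti-ALVAC antibodies between volunteers who acquired HIV infection" and volunteers who stayed uninfected. "Controls will be matched to cases by gender, age and risk behavior at a 2:1 ratio".

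The section states no positivity cut-off, high-titre category, significance level, power or expected seroprevalence.

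**The concern.** The result that prompted the work is about level, and the cited Ad5 method measures level, but the one comparison named for HIV acquisition uses only presence. If risk rises with titre, or sits only at high titres, infected volunteers can have clearly higher titres than controls while the proportions positive are similar. Where most volunteers are positive, there is little room for the proportions to differ at all.

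A null result on prevalence could then be read as showing that pre-existing Ad5 antibody had no bearing on acquisition, when the contrast that raised the question had not been examined. This is more than detail left to an analysis plan: the protocol names its comparison, and that comparison fits its own rationale poorly.

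**Working it through.** **No figure to reproduce.** The protocol gives no power for this study. The nearest stated figures are in section 6.9.4.3, for neutralising antibody at 40% versus 70%: at least 93% power with 43 versus 150 volunteers, and 87% with 33 versus 150. The two-proportion formula gives 94.9% and 90.1%; with continuity correction it gives 92.7% and 86.2%, within a point of the stated figures. The uncorrected test is used below.

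**Inputs.**
- Cases: "approximately 43 infected vaccinees and 78 infected placebo recipients" (section 6.9.3.2), so 43 + 78 = 121. This is the design expectation; the observed number is not given.
- Controls: 2 × 121 = 242.
- Assumed: two-sided 5%, normal log titre, matching ignored.
- Seroprevalence p in controls is not documented, so it is varied.

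**Three risk models, giving the proportion positive among cases (p₁).**
- Graded: log titre in cases is shifted by 0.30 SD, so p₁ = Φ(Φ⁻¹(p) + 0.30).
- High titre only: odds ratio 2 in a share h of volunteers (the top third, or the top half of positives if that is smaller), so p₁ = (p − h + 2h)/(1 − h + 2h).
- Presence only: odds ratio 2, so p₁ = 2p/(1 + p).

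**Prevalence test in closed form.** Power ≈ Φ[(p₁ − p − 1.96·SE₀)/SE₁], where SE₀ is the pooled and SE₁ the unpooled standard error.
- Graded, p = 50%: p₁ = Φ(0.30) = 0.618, SE₀ = 0.0555, SE₁ = 0.0546. Power = Φ[(0.1179 − 0.1088)/0.0546] ≈ 57%.
- Graded, p = 85%: p₁ = 0.909, SE₀ = 0.0375, SE₁ = 0.0348. Power = Φ[(0.0593 − 0.0735)/0.0348] ≈ 34%.
- High titre only, p = 50%: h = 25%, p₁ = 0.75/1.25 = 0.60, SE₀ = 0.0555, SE₁ = 0.0549. Power = Φ[(0.100 − 0.1088)/0.0549] ≈ 44%.
- High titre only, p = 85%: h = 1/3, p₁ = 0.8875, SE₀ = 0.0383, SE₁ = 0.0368. Power = Φ[(0.0375 − 0.0751)/0.0368] ≈ 15%.

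**Simulated power.** The prevalence test is set against a Mann-Whitney test on titre with undetectable values tied. Values are percentages and carry simulation error of about a point or two.

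| Risk model | Seropositive | Prevalence | Titre | Lost by prevalence only |
|---|---|---|---|---|
| Graded, 0.30 SD | 10% | 41.0 | 43.0 | 2.0 |
| | 20% | 52.4 | 55.3 | 2.9 |
| | 50% | 55.9 | 67.9 | 12.0 |
| | 85% | 35.3 | 75.3 | 40.0 |
| High titre only, OR 2 | 10% | 22.7 | 24.4 | 1.7 |
| | 20% | 36.4 | 42.9 | 6.5 |
| | 50% | 43.9 | 69.5 | 25.6 |
| | 85% | 15.6 | 73.6 | 58.0 |
| Presence only, OR 2 | 10% | 58.3 | 58.3 | 0.0 |
| | 50% | 85.2 | 77.1 | −8.1 |
| | 85% | 46.6 | 19.1 | −27.5 |

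The closed-form values agree with the simulated prevalence column to within about a point.

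**The case against.** The strongest objection is that presence may be the right exposure. Section 6.9.7 words the mechanism as prior immunity, and the high-level result came from recipients of an Ad5 vector, whereas this trial's vector is canarypox. If presence carries the risk, a titre test is the weaker one, by 8 points at 50% seropositive and 27.5 at 85%. This stands. A reader might infer that titre should replace prevalence; the protocol's wording does not support that, because it leaves both risk models open.

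A second objection is that the size rests on quantities the documents do not give. This also stands. A reader might infer a guaranteed minimum loss, but at 10% seropositive the loss is about 2 points or less in all three models.

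Third, a reader might extend the point to anti-ALVAC antibody, and to the immunogenicity comparison in about 150 vaccinees, which is also set up as "geometric mean binding antibody by presence or absence of pre-existing anti-ALVAC antibody". The documents state no hypothesis about level for anti-ALVAC, and no loss has been computed for that comparison, so neither is part of this point.

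Fourth, a reader might say that a null here would hide an imbalance between arms. The 200-sample component also serves that question, and it is not worded as present or absent. The case-control study has its own aim, the effect on acquisition.

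Finally, this is a short statement of intent for exploratory work on stored samples, and nothing in it forbids analysing titres. That limits the importance of the point, but does not explain why the one comparison named leaves out the contrast that prompted it.

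**Conclusion.** The point holds for Ad5, as a mismatch between rationale and comparison. With prevalence as the only comparison, the study cannot tell a just-detectable from a high titre.

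The cost is conditional. It is negligible if few volunteers are seropositive. It is substantial (about 12 to 26 points) if half are and risk rises with titre, and severe (about 40 to 58 points) at 85%. It is nil or reversed if presence alone matters. These figures assume 121 cases, 242 controls, a two-sided 5% test, normal log titre, an effect of 0.30 SD or odds ratio 2, and no allowance for matching.

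Because neither seroprevalence nor the form of the risk is known, relying on one dichotomy is fragile. The matter is minor: the analysis is exploratory and the efficacy conclusion does not depend on it.

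**What to change.** In section 6.9.7:

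1. Keep the prevalence comparison and define the cut-off for a positive result.
2. For Ad5, add a pre-specified comparison of baseline titre between cases and controls. Use either log10 titre with undetectable values set at the detection limit, or negative/low/high categories with the boundary fixed before case status is linked.
3. Analyse both in a way that respects the 2:1 matching, for example by conditional logistic regression.

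The assay and plasma are those already planned, provided the quantitative reading is kept.

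The price is a second exploratory test. If multiplicity is controlled, some power is lost. With a Bonferroni split (critical value 2.24), the prevalence test in the graded case at 50% seropositive falls from about 57% to Φ[(0.1179 − 2.24 × 0.0555)/0.0546] ≈ 45%. Reporting both as exploratory, with confidence intervals and no formal correction, avoids that loss but gives weaker protection against a chance finding. The protocol should say which is intended.
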